**Fig. 3 Fig3:**
[figure not shown]
Overview of UPAVAN intervention components in each arm

NSA and nutrition-specific practices for UPAVAN are based on formative research undertaken by the UPAVAN team (focus group discussions, transect walks, and a seasonal calendar) [45] and the available global and local evidence. The UPAVAN team then prioritise the practices to promote in the interventions based on the following criteria: local relevance and acceptability, feasibility of adoption by participants, potential for uptake, and hypothesised impact on dietary diversity and nutritional status of mothers and children in the local context. A sample list of video and meeting topics, with rationale for the NSA topics, is provided in Additional file 1.

All arms, including the control arm, receive any services provided by the government or other non-governmental organisations. As a benefit to all participants, government frontline nutrition and health workers (Anganwadi workers and Accredited Social Health Activists) in all arms, including the control, receive a residential 2-day training course in maternal, infant, and young child nutrition.

##### Common features of all intervention arms

All intervention arms receive the following:Two facilitated group meetings per month per group over 32 months, of varying content between arms, that are run by local, trained, paid facilitators.In at least half of the meetings (all meetings in AGRI; half of the meetings in AGRI-NUT and AGRI-NUT+PLA), groups will view and discuss NSA videos on a pre-defined set of prioritised practices.Follow-up visits to all participating pregnant women and mothers of children aged 0–23 months after each video viewing, or PLA meeting where applicable. The purpose of these visits is to maintain rapport with the participant, check if the participant recalls or has adopted the key practices discussed in the video, reinforce messages shown in the videos and clarify if needed, when relevant strengthen the link between participants and community frontline workers, and encourage attendance at the next meeting.

##### Distinguishing features

The distinguishing features between arms are as follows:*AGRI*. Women’s groups view and discuss two NSA videos each month, following the foundational approach.*AGRI-NUT*. Women’s groups view and discuss two participatory videos each month, following the foundational approach but with 50% of the videos covering NSA topics (half of the videos shown in the AGRI arm) and 50% covering nutrition-specific behaviour change topics.*AGRI-NUT+PLA*. Each month, women’s groups view one NSA video (half of the videos from the AGRI arm) and have one PLA meeting on nutrition-specific topics. Some of these PLA meetings are discussion-based and some are facilitated disseminations of videos on nutrition-specific topics. The videos produced in this arm arise out of relevant discussions from the PLA meetings and so are different from the nutrition-specific videos in AGRI-NUT that use the foundational approach of identifying content described earlier. Facilitators will also only conduct follow-up visits when relevant — that is, after all NSA videos and PLA meetings that contain clear nutrition-specific messages.

The linkages between the foundational model and the PLA cycle are illustrated in Fig. 4.

**Fig. 4 Fig4:**
[figure not shown]
Illustration of how the four phases of the Participatory Learning and Action cycle feed into the foundational approach of facilitated video dissemination in groups in AGRI-NUT+PLA

The PLA cycle comprises four phases. In the first phase, group members identify and prioritise locally salient maternal and child nutrition problems by discussing local practices using games and picture cards. In the second phase, they explore the causes and effects of the prioritised problems using storytelling and discussions. Groups plan locally feasible strategies to address the problems, decide on roles and responsibilities for implementing the strategies, and share their learning with the wider community. In the third phase, groups implement their strategies. In the fourth phase, groups informally evaluate their achievements and plan for the future. The PLA cycle is embedded into the group-based video dissemination and follow-up visits approach described above, so that the discussions in the PLA group meetings inform the content of nutrition-specific videos in arm 3 (AGRI-NUT+PLA).

#### Intended coverage

For the video disseminations (including videos from the PLA cycle), there will be approximately five to six women’s groups per 1000 population, with each group comprising approximately 20–25 members. Where possible, groups will be formed by linking existing women’s SHGs, typically merging two SHGs to create one video-viewing group. Where SHGs do not exist, new women’s groups will be formed. For the PLA group meetings, there will be two women’s groups per 1000 population, or more where clusters include remote hamlets or demand is high.

Although we plan to conduct fortnightly group meetings, we have also planned for some implementation breaks due to festivals and seasonal and logistical factors. We plan to implement a minimum of 54 meetings per group over the 32-month implementation period.

Pregnant women and mothers with children 0–23 months (1000-day period) who have attended the meetings will receive a follow-up visit. Other women in the 1000-day period who are not attending will be identified by facilitators through communication with the Anganwadi worker and encouraged to attend.

The outline of nutrition-sensitive and nutrition-specific intervention topics, inputs, processes, and the mechanisms by which the interventions are hypothesised to affect dietary diversity and nutritional status is described in the theory of change in Fig. 5.

**Fig. 5 Fig5:**
[figure not shown]
UPAVAN theory of change

### Impact evaluation

The impact of the interventions will be evaluated through repeat cross-sectional household surveys at the same time of year (November to January) at baseline (2016–2017) and endline (2019–2020), in the same intervention and control clusters.

#### Trial outcomes

The primary outcomes are:Percentage of children (6–23 months of age) consuming ≥ 4 out of 7 food groups per day, based on a 24-h dietary recall answered by the mother or female primary caregiverMean maternal BMI (kg/m^2^) of non-pregnant, non-postpartum (gave birth > 42 days ago) mothers or female primary caregivers of children aged 0–23 months

Secondary outcomes are:Percentage of mothers or female primary caregivers consuming ≥ 5 out of 10 food groups per day, based on a 24-h dietary recallPercentage of children with a weight-for-height z-score < -2 SD

Maternal BMI and child wasting are selected as outcome measures of chronic energy deficiency for adults and acute undernourishment for children. Both indicators predict mortality and morbidity [46, 47], vary seasonally so may change within the intervention timeframe, and are globally used so facilitate comparisons with other studies [47].

Dietary diversity scores for adults and children are selected as validated indicators of dietary adequacy of multiple micronutrients [48, 49]. These scores capture short-term dietary improvements; thus, they may also be amenable to change within the timeframe of this trial. Indicators for maternal and child actute malnutrition [50–53], women’s time use [54], and household agriculture production [55] are also included.

All trial outcomes are listed in Table 2.

**Table 2 Tab2:** UPAVAN trial outcomes

Outcome	Indicator
*Primary outcomes*	
Child dietary diversity	• Percentage of children (6–23 months of age) consuming ≥ 4 out of 7 food groups per day (assessed by 24-h recall answered by the mother or female primary caregiver)
Maternal underweight	• Mean body mass index (BMI) (kg/m^2^) of non-pregnant, non-postpartum (gave birth > 42 days ago) mothers or female primary caregivers of children aged 0–23 months
*Secondary outcomes*	
Maternal dietary diversity	• Percentage of mothers or female primary caregivers consuming ≥ 5 out of 10 food groups per day (24-h recall) [50]
Child wasting	• Percentage of children (aged 0–23 months) who are wasted (weight for height < -2 SD)
*Other outcomes*	
Maternal wasting	• Percentage of pregnant and non-pregnant mothers or female primary caregivers with mid-upper arm circumference (MUAC) < 230 mm [51]
Child acute malnutrition	• Percentage of children (aged 6–23 months) with acute malnutrition (MUAC < 125 mm) [52]
Maternal and child haemoglobin (Hb) concentrations	• Mean Hb (g/dl) of children (6–23 months of age)
	• Mean Hb (g/dl) of non-pregnant mothers or female primary caregivers
Infant and young child feeding practices	• Percentage of children (aged 6–23 months) receiving the World Health Organization-recommended Minimum Acceptable Diet [53]
Women’s decision-making	• Percentage of women ‘empowered’ in women’s decision-making in productive and health-related domains, aggregated, measured using the Women’s Empowerment in Agriculture Index
Women’s time use	• Percentage of women ‘empowered’ in the women’s time use domain of the Women’s Empowerment in Agriculture Index [54]
Gender parity in agriculture	• Percentage of women achieving gender parity between themselves and a male household member, defined using the Women’s Empowerment in Agriculture Index
Household economic status and food security	• Mean per capita household share of food expenditures
	• Mean per capita total household expenditures
Household agriculture production	• Mean production diversity (count of the number of crops or livestock produced) [55] • Total value of agricultural production • Net value of agricultural production (= *value of agricultural production – costs*)

#### Sample size

The trial has 148 clusters, allocated in the ratio 1:1:1:1 (Control: AGRI: AGRI-NUT: AGRI-NUT+PLA), with on average 32 mother-child dyads (children aged 0–23 months; including 24 mother-child dyads aged 6–23 months) per cluster, giving a total sample size of 4736 mother-child dyads. Assuming a conservative intra-cluster correlation of 0.06, based on data from a trial conducted in Keonjhar [56], this sample size has 80% power with a 5% level of significance to detect a 9% absolute difference in child dietary diversity [57] between each intervention arm separately and the control arm, assuming a baseline of 22% of children with minimum dietary diversity (consumption ≥ 4 out of 7 food groups in the last 24 h [58]), and would allow us to detect a difference in mean maternal BMI of 0.3 kg/m^2^ [59] between each intervention arm separately and the control arm [60]. As the analysis will be restricted to comparisons between each intervention arm and the control arm, no adjustments were made for multiple comparisons.

#### Blinding

As with most interventions of this nature, participants cannot be ‘blinded’ to allocation status. Information on allocation of clusters to the respective implementation teams (the implementation team of Digital Green, VARRAT, and Ekjut including the project manager, project coordinator, arm coordinators, supervisors, video production teams, and facilitators) were only given after the initial NSA and basic nutrition training was given to the facilitation team. To minimise any contamination of nutrition-specific messages or PLA components across the arms, group facilitators and their supervisors, overseen by an arm coordinator, will not work across arms, and the arm-wise review meetings with the implementing teams will be held separately. The data manager conducted the randomisation, but the data collection team, principal investigator, and trial statistician are blinded to allocation. The trial statistician will conduct final analyses blinded to allocation.

#### Data collection and management

Before the baseline survey, a team of trained enumerators conducted a census in all 148 clusters, using standardised and documented procedures, to list all households with a child aged 0–23 months. In each cluster, well-trained data collectors invited a random sample of eligible households to participate in the survey and obtained individual written informed consent from participants.

The household survey comprised questionnaires for women and men (available in Additional file 2). Mothers or female primary caregivers were interviewed about nutrition, health, and empowerment in agriculture. Height, weight, mid-upper arm circumference (MUAC), and haemoglobin measurements were taken for each mother-child dyad. A male household member (if possible the caregiver’s husband, otherwise a male decision-maker, or a female decision-maker in a female-only household) was interviewed about agriculture and household socio-economic status. In addition, due to the length of the questionnaire and to reduce the burden on respondents, half of the male participants, randomly selected, were asked questions on their empowerment in agriculture while the other half were asked about household consumption and expenditure. The questionnaires were pilot tested before use.

Data collectors, ‘lab technicians’ (certified to take blood spots), and supervisors were organised into teams and collected data over the 3 months prior to implementation start; this will be repeated for 3 months for the endline survey. Supervisors and lab technicians took anthropometric measurements, and data collectors conducted the rest of the interview. Before data collection, measurements of maternal and child height, MUAC, and haemoglobin concentrations by supervisors and lab technicians were standardised against a ‘gold standard’ measurer, and we calculated inter- and intra-technical error of measurement and re-trained weaker teams. Data collectors were given 3 weeks of training, and we standardised the child dietary diversity score by comparing data collectors against a ‘gold standard’ interviewer.

Child length was measured using Seca 417 Infantometers, adult height using Seca 213 Stadiometers, maternal and child weight using PLAX-Cruzer scales, MUAC using MUAC tapes for children and Seca head circumference tapes for adults, and haemoglobin concentrations using HemoCue Hb 301 machines. Severely undernourished children (MUAC < 115 mm and/or bilateral pitting oedema) or mothers (MUAC < 210 mm or haemoglobin < 7 g/dl) were advised to consult the government frontline nutrition worker or Anganwadi worker for referral. Scales were calibrated weekly, and the stadiometers, infantometers, and HemoCues were calibrated at the start, middle, and end of the survey period. These procedures will be repeated at the endline survey.

The Quality Assurance team completed observation checklists on 10% of households to ensure that teams adhered to protocols, and they took duplicate readings on a subset of questions by revisiting 20% of households to check consistency.

For baseline, anthropometric data were entered using tablets (iBall Slide Snap 4G2) and transferred to a password-protected computer at the field office each day, and the rest of the survey was conducted on paper forms that were stored in a locked office. We reviewed the quality of anthropometric data by checking plausibility of values, digit preference, and missing values. Paper forms were submitted to the Quality Assurance team at the field office for a review of the logic, completeness, and plausibility of values, and errors were resolved by discussion with the data collector or revisit to the household. Data from paper questionnaires were double entered by trained data operators and discrepancies resolved by referring to the original source document.

The same procedures will be applied for the endline survey, although we plan to use tablets for all data capture.

The study team will make the full datasets available in anonymised form within 3 years of project completion. Before depositing into the data repository (LSHTM Data Compass, an institutional research data repository), data will be anonymised to protect participant confidentiality and converted into a file format suitable for long-term access, based on the recommendations of the UK Data Service [61]. The results will be published in a peer-reviewed journal.

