## Background

Maternal and child undernutrition are among the world’s most serious health, economic, and human development challenges. Undernutrition contributes to around 3.1 million (45%) child deaths annually [1]. In South Asia, more than a third of children are stunted and a third of women are underweight [2]. Maternal and child undernutrition have adverse consequences for pregnancy outcomes, children’s morbidity and mortality, their physical and cognitive development, and the incidence of chronic diseases in adulthood [3]. The impacts of undernutrition also extend beyond health, with negative consequences for educational attainment, economic productivity as adults, and human wellbeing [4].

India has made progress in reducing undernutrition, but the prevalence of child undernutrition remains strikingly high: 38% of children under 5 years of age are stunted (height-for-age z-score < -2 standard deviations, SD), 21% are wasted (weight-for-height *z*-score < -2 SD), and 58% are anaemic [5]. In addition, almost a quarter of Indian women aged 15–49 are underweight and more than half are anaemic [6].

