### Study design

The study is a four-arm, cluster randomised controlled trial with 148 clusters randomly allocated to the four trial arms to give 37 clusters per arm (allocation ratio 1:1:1:1). The trial will run for a total of 53 months, from December 2015 to May 2020, including intervention development, setup, baseline and endline surveys, and intervention implementation for 32 months (from March 2017 to October 2019). The impact of the interventions will be assessed by repeat cross-sectional surveys of eligible households at baseline (November 2016 to January 2017) and endline (November 2019 to January 2020).

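### The printed survey referral rule acts on low haemoglobin in mothers but sets no haemoglobin trigger for children, although haemoglobin is measured in both

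*Protocol article*

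**What the plan says.** Under Data collection and management, the protocol article sets out the referral rule with numerical criteria for two groups: "Severely undernourished children (MUAC < 115 mm and/or bilateral pitting oedema) or mothers (MUAC < 210 mm or haemoglobin < 7 g/dl"). Anyone meeting a criterion is told to consult a government frontline worker for referral. For children the criteria are MUAC and oedema. For mothers they are MUAC and haemoglobin.

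The same section states that "haemoglobin measurements were taken for each mother-child dyad", and lists one device for both members of the dyad: "haemoglobin concentrations using HemoCue Hb 301 machines". The paragraph holding the referral rule closes with "These procedures will be repeated at the endline survey". Table 2, under Trial outcomes, lists child haemoglobin among the other outcomes: "Mean Hb (g/dl) of children (6–23 months of age").

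**The concern.** The survey team obtains a haemoglobin value for the child at the visit, and the printed rule attaches no action to it. A very low value in the mother leads to advice. The same value in her child does not, unless the child also has a MUAC below 115 mm or oedema. The sentence itself treats low haemoglobin as a form of severe undernourishment in mothers, so describing the group as severely undernourished does not explain leaving it out for children. No reason for the difference is given.

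What is at stake is the safety of the surveyed children, not the analysis. Low child readings are to be expected: the Background says of Indian children under 5 that 38% are stunted, 21% are wasted "and 58% are anaemic". That anaemia figure covers all severities. Baseline is finished, so only the endline survey can still change.

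**Working it through.** The point rests mainly on reading the text. The arithmetic only gives its scale, and no figure in the plan is in dispute.

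**The rule set against the measurements**

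| | Children | Mothers |
|---|---|---|
| MUAC measured | yes | yes |
| MUAC referral trigger | < 115 mm | < 210 mm |
| Oedema trigger | bilateral pitting oedema | none printed |
| Haemoglobin measured | yes | yes |
| Haemoglobin referral trigger | none printed | < 7 g/dl |
| Haemoglobin listed as an outcome | yes, 6–23 months | yes, non-pregnant |

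**Search for a child trigger elsewhere.** The Adverse events section describes quarterly compilation of severe events, review by the principal investigator for relatedness, and annual review by the independent statistician on the Trial Steering Committee. It contains no haemoglobin action level and no referral route from the survey. No other section supplies one.

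**Can MUAC stand in for haemoglobin?** The document gives no basis for assuming so. Table 2 treats child acute malnutrition by MUAC and child haemoglobin as separate outcomes.

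**Scale.** The inputs come from the Sample size section: 148 clusters, 37 per arm, and on average 32 dyads per cluster, "including 24 mother-child dyads aged 6–23 months". These are planned averages, not ceilings.

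- All dyads: 32 × 148 = 4,736, which reproduces the stated total (32 × 37 = 1,184 per arm).
- Children aged 6–23 months: 24 × 148 = 3,552 (24 × 37 = 888 per arm).

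Which count applies depends on who is actually tested. The text says each dyad, giving 4,736. The outcome definition covers only 6–23 months, which would give 3,552.

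**Children affected.** The document does not give the prevalence of severe anaemia in children, so the number missed cannot be derived. As a scale factor only, for each 1 percentage point of severe anaemia:

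- Whole survey: 3,552 × 0.01 = 35.5 and 4,736 × 0.01 = 47.4, so about 36 to 47 children.
- Per cluster: 24 × 0.01 = 0.24 and 32 × 0.01 = 0.32.

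Children who would already be advised on MUAC or oedema have to be subtracted from these figures. Their number is not given either.

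**The case against.** The strongest objection is that this is a journal article condensing a fuller protocol. Referral thresholds normally sit in survey manuals and ethics papers that are not shown, so a clause may simply have been lost in shortening. The sentence is in the past tense, sits among equipment and calibration details, and does not say that its criteria are exhaustive. The statement about repetition at endline directly follows the calibration sentence and may refer chiefly to that. The prevalence of severe anaemia is unknown, and the 58% figure is national and covers any severity. The maternal threshold has no stated justification for infants. Frontline workers serve, and receive nutrition training in, every arm.

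Much of this stands as a limit on the claim. It cannot be said that any child went unreferred at baseline, the number affected is unknown, and 4,736 applies only if infants under 6 months are tested too. The condensation argument does not dispose of the point, however. The article did not leave the rule to another document: it printed numerical thresholds for both groups and included haemoglobin for one of them. The closing sentence about endline reads most naturally as covering the whole paragraph. Training frontline workers does not replace a trigger that sends a particular child to them.

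**Conclusion.** The concern holds. As printed and carried forward to endline, the rule gives no referral advice to a severely anaemic child with a MUAC of 115 mm or more and no oedema, although that child's haemoglobin has just been read. The gap covers 3,552 to 4,736 planned child readings, depending on whether children under 6 months are tested. The number of children who would need advice cannot be derived.

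The conclusion assumes that the printed criteria are the ones applied and that the endline statement includes them. Confidence is medium because a field document that is not shown may contain a child trigger. The gap is identical in all arms and biases no comparison, so the change is advisable on safety grounds and is not needed for the validity of the trial.

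**What to change.** Before the endline survey ("endline (November 2019 to January 2020")), add a haemoglobin referral criterion for every child whose haemoglobin is measured, worded identically for all arms. Parity with the maternal value of 7 g/dl should be the floor. The investigators and ethics committees should set the final threshold, since the document gives no basis for choosing one for this age group. If a child trigger was already used in the field, correct the sentence to state it.

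The cost is one extra criterion applied to a value already read at the visit, using the referral route already in place, or one corrected sentence. If severe anaemia means falling below the chosen threshold, extra referrals would be about 0.24 to 0.32 per cluster for each percentage point of severe anaemia. A higher threshold would add more. Advice is given after the endline measurement and under the same rule in every arm, so no outcome comparison is affected.
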